### Secondary Objectives

The secondary objectives will be (1) to study the association between the executive functioning and theories of mind of school-age children and (2) to study the association between parental anxiety and theories of mind of school-age children.

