## Hypotheses

A developmental delay or deficit in the theory of mind in school-age children born prematurely compared to that in school-age children born full-term is expected. This delay or deficit is thought to be related to executive dysfunction and/or the level of parental anxiety.

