#### Sample Size

Because of lack of literature, sample size calculation could not be performed on association between theories of mind and prematurity. Because of link between verbal skills and TOM has been shown in several studies that highlighted the impact of verbal skills on TOM task performance (47, 48), the calculation of the number of subjects required was performed for association between prematurity and WISC VCI with the following hypotheses: an average VCI score for “control” patients of 103.2 ± 12.6 (49) and an average VCI score for “preterm” patients of 92. With an alpha risk of 5%, a power of 90%, and a bilateral test, the number of patients required was 28 per group (NQuery software version 4.0).

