#### Statistical Analysis

Descriptive analysis will be performed. Quantitative variables will be expressed as the mean± standard deviation or median (range) and qualitative variables as number (percentage).

Factors associated with development of the affective and cognitive theories of mind separately, notably groups (“preterm”/“full-term”) and parental anxiety, will be studied using univariate analysis (Wilcoxon tests for qualitative variables and Spearman's correlation tests for quantitative variables) and multivariate analysis (linear regression with variables with a *p* < 0.10 by univariate analysis included).

The association between executive functions, evaluated using NEPSY-II, and the development of theories of mind will be studied using univariate analysis (Wilcoxon tests for qualitative variables and Spearman's correlation tests for quantitative variables) and multivariate analysis (linear regression with variables with a *p* < 0.10 by univariate analysis included).

The association between the executive functions, evaluated using the TEA-CH, and the development of the theories of mind will be studied using univariate analysis (Wilcoxon tests for qualitative variables and Spearman's correlation tests for quantitative variables) and multivariate analysis (linear regression with variables with a *p* < 0.10 by univariate analysis included).

A *p* < 0.05 will be considered significant. Statistical analysis will be performed using SAS (Version 9.4, SAS Institute, Cary, NC, USA).

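### The executive-function associations with theory of mind are tested without group or age fixed in the analysis, so the preterm/full-term difference alone can produce an association

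*Protocol article*

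**What the plan says.** The first secondary objective is "to study the association between the executive functioning and theories of mind of school-age children", stated for the children as a whole and not by group. The Statistical Analysis section gives each test battery its own paragraph. For the first: "The association between executive functions, evaluated using NEPSY-II, and the development of theories of mind will be studied using univariate analysis". For the second: "The association between the executive functions, evaluated using the TEA-CH, and the development of the theories of mind will be studied" in the same way. Univariate means a Wilcoxon test or a Spearman correlation. The multivariate step is a linear regression containing whatever reached p < 0.10 univariately, and significance is judged at 0.05. Neither paragraph mentions group, age or a within-group analysis.

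The paragraph before these covers factors associated with theory of mind. It names group and parental anxiety together as candidates under the same p < 0.10 rule.

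The Hypotheses section expects "A developmental delay or deficit in the theory of mind in school-age children born prematurely" relative to full-term children, and the Introduction reports that premature children have difficulty on executive tasks. Age and sex are matching factors (Participants and Procedure for Recruitment), but neither is named in the analysis section.

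**The concern.** Half the sample is recruited because it is preterm. If preterm children score lower on both executive tasks and theory of mind, pooling the groups gives two clouds of points displaced along the same diagonal. A correlation then appears even if executive function is unrelated to theory of mind among preterm children and among controls. A regression without group inherits the same artefact.

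The Hypotheses section attributes the expected deficit to executive dysfunction and/or parental anxiety, and the Discussion would use the results to target therapeutic actions. A significant pooled association could be read as support for that explanation when it only restates that preterm children score lower on both measures.

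**Working it through.** **Inputs from the article (Sample Size).** "the number of patients required was 28 per group", so N = 56. Control VCI: "an average VCI score for “control” patients of 103.2 ± 12.6". Preterm VCI: "an average VCI score for “preterm” patients of 92". Design: "With an alpha risk of 5%, a power of 90%, and a bilateral test". No group gap is given for theory of mind, executive function or anxiety, so those gaps are assumptions below.

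**The plan's own figure.** Difference 103.2 − 92 = 11.2; standardised 11.2/12.6 = 0.89. Normal approximation: n = 2 × (1.960 + 1.282)² × (12.6/11.2)² = 26.6, so 27 per group. The noncentral t gives 89.3% power at 27 and 90.4% at 28. The stated 28 per group is reproduced. It concerns VCI and says nothing about the association analyses.

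**Correlation created by pooling.** With equal groups, zero within-group association, and gaps of d₁ and d₂ SD:

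r = (d₁d₂/4) / √[(1 + d₁²/4)(1 + d₂²/4)]

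- 0.5 and 0.5: 0.0625/1.0625 = 0.059
- 0.8 and 0.8: 0.16/1.16 = 0.138
- 0.89 and 0.89: 0.1975/1.1975 = 0.165

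**Approximate false-positive rate.** With Fisher's z, the shift is atanh(r) × √(56 − 3) = atanh(r) × 7.28, compared with ±1.96:

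- 0.059: shift 0.43, rate about 7.1%
- 0.138: shift 1.01, rate about 17.3%
- 0.165: shift 1.21, rate about 22.8%

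**Simulation.** 28 + 28 children, no within-group association, at least 6,000 runs per setting for the pooled Spearman test. Ranges show repeat simulations.

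| Gap on both measures | Pooled Spearman | Screened regression, group not a candidate | Screened regression, group a candidate | Group in the model |
|---|---|---|---|---|
| 0.5 SD | 6.5–7.9% | 6.4–7.3% | 3.8–4.5% | about 5% |
| 0.8 SD | 17–18.3% | 17% | 3.2% | about 5% |
| 0.89 SD | 22.5–23.8% | 22–22.8% | 2.8–3.0% | about 5% |

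With unequal gaps of 0.89 and 0.5 SD, the pooled Spearman rate is about 11–12%.

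**How often the screen drops group.** About 44% of runs at a 0.5 SD gap in theory of mind, and about 6.5% at 0.89 SD.

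**Age, conditional.** If both scores correlate with age at 0.3, 0.4 or 0.5 and there is no group gap, the pooled Spearman rate is 9.4%, 21% or 44–46%. This needs executive scores that are not age-scaled. Where age is a screened candidate, the regression rate falls to 2.4–3.4%.

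**The case against.** **The screen protects the regression where confounding is strong.** This is correct if group is a candidate: a large gap gets group into the model, and a small gap that is often screened out does little harm. A reader might infer that the absence of forcing is itself what inflates the error rate. The figures do not support that. What matters is whether group is in the candidate set, and the executive-function paragraphs do not name it. A condensed article may leave a full candidate list to another document, so a regression without group is one reading and not a certainty. The univariate tests, however, are fully stated and are confounded under any candidate list.

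**Parental anxiety is already handled.** Largely so. A reader might infer that both secondary objectives are equally affected. They are not: group stands beside anxiety as a named candidate, and a screened regression of that form gives about 3–4.5%. Only the univariate anxiety test is exposed.

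**Age is matched, and the executive tests are published batteries.** Matching balances age between groups. It does not remove age from an association across children aged 7–10 years, and the theory-of-mind tasks are unstandardised. But nothing says that raw executive scores will be used, so the high age-related rates cannot be charged to the plan as they stand. There is no evident reason for age to confound parental anxiety.

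**Executive function may mediate the effect of prematurity, so group should stay out.** A mediation claim still requires executive function to predict theory of mind given group. The pooled correlation cannot show that.

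**Separate models by battery.** A reader might count these as an error. The objective asks only for association, and the article promises no mutual adjustment, so this is a design preference.

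**Conclusion.** The point holds for the executive-function analyses. The stated Spearman tests, and the regressions if group is not a candidate, can return an association that reflects only the difference between the groups. The false-positive rate is about 7–8% at gaps of 0.5 SD, 17–18% at 0.8 SD and 22–24% at 0.89 SD, against about 5% with group in the model.

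This rests on three assumptions:

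- The analysis pools all 56 children. This is inferred from the wording of the objectives and the analysis section, which do not state it outright.
- The gaps are illustrative. The 0.89 SD is the article's VCI difference, borrowed here for both measures. It should not be read as the article's expectation for executive function or theory of mind. At 0.5 SD the excess is slight.
- There is no association within groups. The rates describe that null case and do not predict that any finding would be false.

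For parental anxiety the exposure is limited to the univariate test. Age is a conditional further confounder of the executive-function associations only. These are secondary objectives; the comparison of theory of mind between groups is not affected by this point.

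**What to change.** Amend the Statistical Analysis section as follows:

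1. Force group and age (a matching factor) into every executive-function regression, whatever their univariate p-values.
2. Keep group in the parental-anxiety regression regardless of the p < 0.10 screen.
3. Label the pooled Spearman results descriptive, and report within-group coefficients, or coefficients partial on group and age, beside them.
4. State whether the executive scores are age-scaled.

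Only wording changes. The cost is two degrees of freedom and slightly lower power: at N = 56, a model with group and age forced in has about 62% power for a partial correlation of 0.3 and 88% for 0.4.

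Entering both batteries together, forcing in sex or the extrapolated verbal comprehension index, and adding group-by-score interactions are optional. With 56 children, each extra term needs its own justification.

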## Abstract

**Background:** Recent research has identified neuropsychological disorders, specifically executive function disorders, in premature children. Executive functions support goal-oriented mental activity and play a role in the development of social cognition. This underlies the social and emotional behavior of individuals. Parental anxiety is also an important environmental factor that can influence the psycho-emotional development of children.

**Objectives:** The present protocol aims to compare the development of social cognition in school-age children born prematurely to that of school-age children born full-term, and to determine the impact of executive (dys)function and parental anxiety on such development.

**Methods/Design:** In this cross-sectional protocol, 28 prematurely born children aged 7-10 years (“preterm”) and 28 full-term born children aged 7-10 years (“control”) will be included. The “preterm” and “control” groups will be matched for sex and age. The neuropsychological evaluation will include that of non-verbal intellectual efficiency (Raven's colored progressive matrices), verbal level (WISC-IV subtests), and executive functions (NEPSY II subtests and the opposite worlds of TEA-CH). The evaluation of social cognition will be conducted via tests of the theory of cognitive and affective mind. Several dimensions of the level of parental anxiety will be collected through the Spielberg Trait Anxiety Inventory Form Y, Beck Depression Inventory, Social Support Questionnaire-6, Parental Stress Index and, specifically for mothers, the Modified Perinatal Post-Traumatic Stress Disorder Questionnaire.

**Discussion:** The results of this protocol will aid our understanding of the development of social cognition in premature children and to determine the factors that influence such development. This clinical research project, although following a fundamental approach, will have clinical implications because a more precise description of the development of social cognition in this school-age population will make it possible to better determine the cognitive targets of therapeutic actions and to search for predictive indices of the efficacy of practices.

**Trial Registration:**https://clinicaltrials.gov/ct2/show/NCT03007095, identifier: NCT03007095.

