## Discussion

This research will aid the identification of the development of social cognition in premature children and potentially determine the factors that influence such development. It will therefore allow for a better understanding of the possible developmental consequences of prematurity. This clinical research project, while following a fundamental approach, will have applied implications. While many studies have documented the relationship between executive functions and the cognitive theory of mind, very few have understood the relationship between executive functions and the affective theory of mind, let alone in children aged 7-10 years. A longitudinal study by Witt et al. (50) investigates delayed theory of mind development in prematurely born children. As demonstrated by the authors, children born prematurely have overcome their difficulties in ToM around five years old. But compared to this one, our main task specifically measures emotional inference, based on a false belief or a false step. Our goal is to understand the possible difficulties of preterm infants in inferring emotions from the “cognitive” mental states of the characters. In our study, we are interested in what happens later (between seven and ten years old when it comes to articulating the mental states of belief (false belief) or non-intention (false step) to emotions, which to our knowledge has not yet been explored in this population. If there is no direct benefit for the protocol participants, we will nevertheless be able to provide a more accurate description of the development of social cognition in this school-age population. We will attempt to identify environmental and parental factors that may influence the development of social cognition and executive functions in premature children. The knowledge acquired will help to better target possible therapeutic actions in the follow-up of premature children, and better accompany and support parents affected by their child's premature birth. Subsequently, the first avenues of care that may be opened up and the further studies carried out will make it possible to evaluate their relevance and efficiency.

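### No stated model holds executive function and parental anxiety together, so the planned analyses cannot show whether either is linked to theory of mind independently of the other

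*Protocol article*

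**What the plan says.** The Abstract of the protocol article sets the aim "to determine the impact of executive (dys)function and parental anxiety on such development". The Hypotheses section says of the expected theory-of-mind deficit: "This delay or deficit is thought to be related to executive dysfunction and/or the level of parental anxiety".

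The Secondary Objectives are narrower and come as two separate items: "to study the association between the executive functioning and theories of mind of school-age children", and "to study the association between parental anxiety and theories of mind of school-age children".

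The Statistical Analysis section then gives three analyses. Each has its own univariate step and its own linear regression, which takes in variables with univariate p < 0.10.

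- The first concerns factors associated with theory of mind, "notably groups (“preterm”/“full-term”) and parental anxiety, will be studied using univariate analysis".
- The second is introduced with "The association between executive functions, evaluated using NEPSY-II, and the development of theories of mind will be studied using univariate analysis".
- The third repeats the second for the TEA-CH.

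Executive function is not named in the first analysis, and parental anxiety is not named in the second or third. No joint model, mutual adjustment or mediation analysis is described anywhere in the article.

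**The concern.** The Hypotheses and the Abstract put forward two candidate explanations for the same deficit. The article also gives reason to expect them to be correlated. The Introduction describes a direct neurodevelopmental route and an indirect route through parental stress, anxiety and depression, both tied to prematurity. The Discussion adds: "We will attempt to identify environmental and parental factors that may influence the development of social cognition and executive functions in premature children".

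When two predictors are correlated, an analysis containing only one of them picks up part of the other's association with the outcome. Both could then be reported as linked to theory of mind, with nothing in the results to show whether each still matters once the other is held fixed. This affects interpretation, because the Discussion hopes to use the findings both to target therapeutic action for the children and to support their parents.

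The issue lies between the two secondary objectives. It does not concern the separation of NEPSY-II from TEA-CH within executive function.

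**Working it through.** **Inputs from the document.** 28 children per group, so n = 56; significance at p < 0.05; entry to each regression at univariate p < 0.10. The 28 per group is not in dispute. With a VCI difference of 103.2 − 92 = 11.2, SD 12.6, two-sided 5% and 90% power, the two-sample t-test has power 0.893 at 27 and 0.904 at 28 per group.

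**Assumed inputs.** The document gives no correlations, so ranges are used. Executive function (E) and parental anxiety (A) correlate at r_EA = −0.2 to −0.5. Executive function and theory of mind (T) correlate at r_ET = 0.4 to 0.5. Anxiety has no contribution of its own:

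- A = r_EA·E + noise
- T = r_ET·E + noise, with all variables scaled to unit variance

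**What this implies.** The crude correlation of anxiety with theory of mind is r_AT = r_EA × r_ET. It runs from −0.2 × 0.4 = −0.08 to −0.5 × 0.5 = −0.25, so it is not zero. The partial correlation given E has numerator r_AT − r_EA·r_ET = 0.

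**Simulation of the separate Spearman test of anxiety** (n = 56, 6,000 runs per setting):

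| r_EA | r_ET | crude r_AT | anxiety significant |
|---|---|---|---|
| −0.2 | 0.4 | −0.08 | 8.1% |
| −0.2 | 0.5 | −0.10 | 10.4% |
| −0.3 | 0.4 | −0.12 | 13.5% |
| −0.3 | 0.5 | −0.15 | 18.8% |
| −0.4 | 0.4 | −0.16 | 20.4% |
| −0.4 | 0.5 | −0.20 | 28.8% |
| −0.5 | 0.4 | −0.20 | 29.5% |
| −0.5 | 0.5 | −0.25 | 43.0% |

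In a regression containing both E and A, the anxiety term is significant in 4.8% to 5.3% of runs.

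**Check that these rates are power.** For normal data the Spearman correlation is (6/π)·arcsin(r/2), which is 0.239 in size at r = 0.25. Then atanh(0.239) × √53 = 1.78, and the probability of significance is about Φ(1.78 − 1.96) = Φ(−0.18) ≈ 0.43. This agrees with the last row: the rate is what a true crude correlation of that size produces.

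**Does having group in the model help?** The article's first analysis was simulated as written, with group and anxiety screened at p < 0.10 and then regressed (4,000 runs per setting). The executive slope was 0.5, and the groups differed by 0 to 0.8 SD on both factors.

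| Within-group correlation of E and A (size) | Anxiety significant, E absent |
|---|---|
| 0 | about 4% |
| 0.3 | 18% to 22% |
| 0.5 | 45% to 49% |

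With group, E and A all entered together, anxiety is significant in about 5% of runs throughout. Group in the model therefore deals with a link that arises only through prematurity, but not with a correlation within groups.

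**The case against.** Four points can be made in the plan's defence.

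**The article is condensed and its list is open.** The first analysis names group and parental anxiety only as leading examples, and the candidates for each regression are not listed. A joint model is therefore not forbidden. A reader might infer that the plan excludes one; the text does not support that. What stands is that executive function is given two paragraphs of its own and no joint model is stated. Under the p < 0.10 rule, joint entry would in any case depend on the univariate results.

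**The 8% to 43% is not an error rate.** A reader might take it as the chance of a false positive. It is not. In the simulated setting anxiety really is associated with theory of mind, at −0.08 to −0.25, and the second secondary objective asks about exactly that association. This objection holds in full. The error would come only from presenting the crude result as an independent contribution.

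**Adjustment can mislead too.** The same correlations arise if parental anxiety affects executive function, which in turn affects theory of mind. The Introduction and Discussion make that route plausible. Anxiety would then matter, yet its adjusted coefficient would be non-significant in about 95% of studies. A cross-sectional design cannot separate this from confounding. This also holds, so adjusted coefficients must not replace the crude ones.

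**The hypothesis does not promise to apportion.** Its and/or wording allows both factors, and the secondary objectives are answered as written. This lowers the severity. It does not remove the gap against the Abstract's aim of determining the impact of both.

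**Conclusion.** The point holds in a limited form. The separate analyses validly answer the two secondary objectives as crude associations. They cannot show whether executive function or parental anxiety is associated with theory of mind independently of the other, which is what the hypothesis and the Abstract lead the reader to expect.

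The size rests entirely on assumed correlations. With 0.2 to 0.5 (absolute) between the two factors and 0.4 to 0.5 between executive function and theory of mind, a factor with no independent contribution is significant on its own in roughly 8% to 43% of studies of 56 children, against about 5% after mutual adjustment. If the factors are uncorrelated within groups and group is modelled, the two approaches hardly differ (about 4% and 5%).

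This is a modest improvement to the explanatory part of the plan. The main comparison of preterm and full-term children is unaffected.

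**What to change.** Keep the crude analyses for the two secondary objectives. For each theory-of-mind outcome, add one prespecified linear model with these terms, all entered together whatever their univariate p:

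- group;
- a small number of executive-function scores, or one composite of the NEPSY-II and TEA-CH scores;
- one parental anxiety score named in advance, for example STAI trait.

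Report crude and adjusted coefficients with confidence intervals side by side, and use the adjusted ones only for statements about independent contributions. State that a null adjusted coefficient does not exclude an effect of parental anxiety acting through executive function, and that this design cannot tell such an effect from confounding.

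The cost is a few lines of text and one extra regression per outcome on data already being collected. With a composite there are three predictors, which 56 children can support. Standard errors grow by a factor of 1/√(1 − 0.3²) = 1.05 at a predictor correlation of 0.3. Under mediation the adjusted coefficient is only the direct part, which is why the crude result stays beside it.

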##### Verbal Subtests of the WISC-IV

The “similarities” and “vocabulary” subtests of the WISC-IV (28) allow for an extrapolated verbal comprehension index (eVCI) to be calculated. This choice entails to compute a prorata because we only want to assess semantic competences, and not social cognition (or more pragmatic) competences as required by Comprehension subtest. We propose this method in order to focus only on semantic skills competences and to avoid a possible bias in the evaluation of the real skills of the two populations studied in theory of mind assessed through these semantic comptences. The “similarities” subtest includes 23 pairs of words of increasing difficulty and specifically evaluates verbal abstraction. The “vocabulary” subtest contains 24 questions of increasing difficulty for which children must provide a definition.

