##### Executive Functions

Auditory attention and repetition of phrases. Using two 3 min word listening tasks, the “Auditory Attention and Associated Responses” subtest of the NEuroPSYchological Assessment 2nd Edition (NEPSY-II) (29) evaluates selective auditory attention and the ability to maintain it, and the ability to modify and maintain a new rule.

The “sentence repetition” subtest evaluates the child's ability to repeat sentences of increasing complexity and length (17 in total). It allows to assess the verbal working memory capacities.

We preferred the NEPSY auditory attention test to the TEA-CH (Elevator counting) because the NEPSY assesses selective auditory attention as well as higher-level executive components that the TEA-CH does not offer.

Inhibition/flexibility. This task from the Test of Everyday Attention for Children (TEA-CH) consists of two tests and evaluates the inhibition and/or cognitive flexibility skills of a child's verbal response (30). In the first test, the “Same World,“ the child must state as quickly as possible the numbers (1 or 2) as they succeed each other in each box of a course provided on a sheet of paper. In the second test, the “Opposite World,” the child must state ”1“ when he sees a ”2“ and state ”2“ when he sees a ”1“ as quickly as possible throughout the course. Four worlds will follow in succession; one same world, two opposite worlds, and finally one same world.

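### The two executive-function analyses do not guarantee verbal level a place, so an executive link with theory of mind may not be separable from language

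*Protocol article*

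**What the plan says.** The first item under Secondary Objectives is the relation of executive functioning to theory of mind. Statistical Analysis addresses it in two parallel paragraphs, one for NEPSY-II and one for TEA-CH. The first opens: "The association between executive functions, evaluated using NEPSY-II, and the development of theories of mind will be studied using univariate analysis". Each paragraph uses Wilcoxon or Spearman tests and then a linear regression that admits only variables with a univariate p below 0.10. Significance is set at p<0.05. Neither paragraph names verbal level, lists the candidates for the screen, or keeps any covariate regardless of its p value.

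Other sections give verbal level a clear role:

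- Sample Size relies on studies that "highlighted the impact of verbal skills on TOM task performance" and sizes the study on the verbal comprehension index for that reason.
- Verbal Subtests of the WISC-IV leaves out the Comprehension subtest, partly to "avoid a possible bias in the evaluation of the real skills of the two populations studied in theory of mind", and speaks of "theory of mind assessed through these semantic comptences".
- Executive Functions describes auditory attention as word listening, TEA-CH as calling for a verbal response, and says of sentence repetition: "It allows to assess the verbal working memory capacities".
- The cognitive and affective theory-of-mind tasks are stories told to the child.

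**The concern.** The protocol itself identifies verbal skill as something that moves theory-of-mind scores, and it builds a verbal score kept apart from social cognition. Some executive predictors, sentence repetition above all, also depend on language. Verbal skill is then a plausible common cause of predictor and outcome. An analysis that leaves it out can show an executive association with no executive contribution behind it.

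The Hypotheses section expects a theory-of-mind delay to be related to executive dysfunction and/or parental anxiety, and the Discussion hopes to inform therapeutic targets. If a language effect were read as an executive one, secondary objective 1 would support the wrong explanation. The eVCI is available for every child, so the only question is whether its use in these models is fixed or left to a p value.

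**Working it through.** **The plan's own figure.** Sample Size gives a control mean and SD "of 103.2 ± 12.6 (49) and an average VCI score for" a preterm mean of 92, and concludes: "With an alpha risk of 5%, a power of 90%, and a bilateral test, the number of patients required was 28 per group". The difference is 103.2 − 92 = 11.2. By the normal approximation, n = 2 × (1.960 + 1.282)² × (12.6/11.2)² = 2 × 10.51 × 1.266 = 26.6, so 27 per group. The exact two-sided t-test has power 89.3% at 27 and 90.4% at 28. The stated 28 per group reproduces, and N = 56 is used below.

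**Assumptions, not in the documents.** Verbal level correlates b = 0.4 to 0.6 with the executive score and a = 0.3 to 0.5 with theory of mind. The executive score has no effect of its own.

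**Crude correlation induced by language.** It equals a × b. By Fisher's z, the chance of p<0.05 is about Φ(√53 × atanh(ab) − 1.96), plus a negligible lower tail:

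- b = 0.4, a = 0.3: ab = 0.12; 7.28 × 0.1206 = 0.88; about 14%
- b = 0.5, a = 0.4: ab = 0.20; 7.28 × 0.2027 = 1.48; about 31%
- b = 0.6, a = 0.5: ab = 0.30; 7.28 × 0.3095 = 2.25; about 61%

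**Simulation of the planned steps** (2,500 studies per setting). All columns but the third give the share of studies with executive p<0.05. The third gives the share in which the eVCI misses the p<0.10 screen.

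| eVCI reliability; b, a | Spearman alone | eVCI misses screen | Regression, eVCI not a candidate | Regression, eVCI screened | Regression, eVCI forced in |
|---|---|---|---|---|---|
| 1.0; 0.4, 0.3 | 13.5% | 31.6% | 13.6% | 4.2% | 4.8% |
| 1.0; 0.5, 0.4 | 27.2% | 10.2% | 28.4% | 2.6% | 5.1% |
| 1.0; 0.6, 0.5 | 57.2% | 1.4% | 59.5% | 3.4% | 5.6% |
| 0.8; 0.4, 0.3 | 13.7% | 41.2% | 13.8% | 6.2% | 6.4% |
| 0.8; 0.5, 0.4 | 28.3% | 16.9% | 29.7% | 6.3% | 6.5% |
| 0.8; 0.6, 0.5 | 56.5% | 4.8% | 58.8% | 8.3% | 8.6% |

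At reliability 0.85 the screened rates are 4.5%, 5.2% and 6.0%. Adding group and age to a model without the eVCI does not help: the rates are 14.6%, 29.2% and 60.4%.

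**Size of the coefficient.** The true standardised executive coefficient is zero. At reliability 0.85 to 1.0, when the executive score passes the screen and is reported, its mean coefficient is about 0.05 to 0.18. With the eVCI and the executive score both kept in every study, the mean is about 0.00 to 0.07. Most of that gap comes from screening the executive score itself. With the eVCI forced but the executive score still screened, a further run (4,000 studies per setting) gave means of 0.16, 0.10 and 0.05 at reliability 1.0, close to the fully screened values of 0.17, 0.11 and 0.05.

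**The case against.** The strongest reply is that the protocol's own rule already does most of the work. If the eVCI is offered to the p<0.10 screen, it enters whenever confounding is strong, and the false-positive rate of the final model is about what forcing it in would give. That stands. A reader might infer from the 14% to 60% range that the planned regression produces false executive links at that rate. The documents do not support this, because the range applies only if the eVCI is never a candidate, and nothing in the article excludes it. The paragraphs can be read either way.

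A second reply is that the crude Spearman result is not an error. The objective is to study an association, and under a shared verbal cause a crude association truly exists. That also stands; the fault would lie in reading it as an executive effect.

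Third, the language argument is uneven. Sample Size speaks of an impact of verbal skill, not of verbal skill governing the scores. Auditory attention is a listening task, and the TEA-CH response is one of two number words. Sentence repetition carries the main load. Nothing in the article ties non-verbal ability to theory of mind, and children with an IQ below 80 are excluded, so a demand to force Raven's score in has little support.

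Fourth, covariate lists are commonly left to an analysis plan. This reply is only partly right. The article does not merely omit a list; it fixes a data-driven entry rule that guarantees nothing a place, against a rationale that it states itself.

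**Conclusion.** The point holds in a limited form. The plan leaves adjustment for verbal level to a p value, although the protocol gives its own reason to fix it. The size depends on a choice that the article does not make: about 14% to 60% false executive links if the regressions hold only executive scores, and about 3% to 7% if the eVCI is screened (up to about 8% at reliability 0.8).

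In the second case two weaknesses remain. The executive coefficient, when reported after screening, averages about 0.05 to 0.18 against a true value of zero. The eVCI also misses the screen in 31% to 41% of studies when its correlation with theory of mind is 0.3.

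All of this rests on assumed correlations, on N = 56, and on language being the only link between the two scores. It concerns a secondary objective and does not show that the planned regression is invalid. It shows that a better rule is available at little cost.

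**What to change.** In the NEPSY-II and TEA-CH paragraphs of Statistical Analysis:

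1. Name the eVCI as a prespecified covariate in both regressions on theory of mind, kept whatever its univariate p.
2. Report the eVCI-adjusted executive coefficient with its confidence interval for every executive score, whether or not its crude test passes p<0.10. Forcing in the eVCI alone would leave the selection bias in the coefficient.
3. Label the Spearman results as unadjusted, and show crude and adjusted estimates side by side.
4. Rest any claim of an executive link independent of language on the adjusted estimate.
5. Optionally, add Raven's score in a sensitivity analysis.

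The cost is a change of wording and one more model term, with no new data or visits. Where verbal and executive skill truly overlap, the adjusted estimate is conservative and some power is lost. This matters most for sentence repetition, which the protocol treats as verbal working memory, and it is the reason to show both estimates.
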